## Discussion

The EXCITE trial protocol is focused on patients undergoing cardiac catheterization with stable CAD and hemodynamically significant coronary artery stenosis. According to previous data, there is still uncertainty whether ET increases the coronary collateral circulation. One critical point of previous studies is the angiographic evaluation of collateral vessels only. Therefore, the invasive measurement of the FFR-based CBF is a functional approach with higher accuracy to assess collateral vessels. This might help to differentiate even small effects of the several therapies. So far, FFR-based evaluation of CBF has only been reported in non-randomized trials.

The EXCITE trial is designed as an all-comers study without specific subgroup exclusion in order to receive generalizable results. For more detailed insight, we pre-defined several subgroups.

Nevertheless, within this study two different training programs can be compared with a sedentary control group. This might help to find the most effective training program in patients with stable angina pectoris and significant coronary stenosis. Because of the lack of previous data investigating the CBF, the present study was designed as a proof-of-concept-trial. Therefore, a valid power calculation was not possible.

Blinding to avoid bias might have been beneficial. However, we implemented methods to reduce bias, such as the use of a central computerized randomization system and a blinded MRI and IVUS core laboratory.

To the best of our knowledge, this is the first randomized study comparing the CBF in patients after high- and moderate-intensity 4-week physical exercise training programs compared to OMT only.

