**Methods/design:**

The EXCITE trial is a three-armed randomized, prospective, single-center, open-label, controlled study enrolling 60 patients with stable CAD and at least one significant coronary stenosis (fractional flow reserve ≤0.75). The study is designed to compare the influence and efficacy of two different 4-week ET programs [high-intensity interval trainings (IT) versus moderate-intensity exercise training (MT) in addition to OMT] versus OMT only on collateral blood flow (CBF). The primary efficacy endpoint is the change of the CBF of the target vessel after 4 weeks as assessed by coronary catheterization with a pressure wire during interruption of the antegrade flow of the target vessel by balloon occlusion. Secondary endpoints include the change in plaque composition as assessed by intravascular ultrasound (IVUS) after 4 weeks, myocardial perfusion as analyzed in MRI after 4 weeks and 12 months, peak oxygen uptake (V02 peak), change in endothelial function and biomarkers after 4 weeks, 3, 6 and 12 months. The safety endpoint addresses major adverse cardiovascular events (death from cardiovascular cause, myocardial infarction, stroke, TIA, target vessel revascularization or hospitalization) after 12 months.

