### Primary and secondary outcomes

The primary study endpoint of the EXCITE trial is the change in the coronary CBF index after 4 weeks of therapy among the three treatment groups (Table 1).

**Table 1 T1:** Primary and secondary endpoints

**Primary**	**Change in CBI after 4 weeks of treatment**
Secondary	1. Change in plaque morphology by virtual
	histology at 4 weeks as assessed by IVUS
	2. Change in myocardial perfusion at 4 weeks and
	12 months as assessed by adenosine MRI
	3. MACE at 1, 3, 6 and 12 months
	4. Hospitalization due to cardiovascular causes
	5. Change in atherosclerotic parameters (hs-CRP,
	ADMA, endostatin, EPC, ox LDL, cytokines,
	adiponectine), lipid status and glucose status
	6. Change in exercise capacity (ergospirometry) and
	V0_2_ peak

The secondary endpoints include the change in the tissue composition of the target lesion after 4 weeks of exercise training compared to optimal medical therapy only.

Other secondary endpoints are displayed in Table 1. To confirm a potential advantage by long-term follow-up, a 12-month follow-up will be performed in the course of the secondary endpoint evaluation.

Safety assessment includes bleeding complications related to the invasive measurement of the CBF according to the GUSTO criteria [45], stroke and renal failure.

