### Measurement of the coronary collateral circulation

The primary study endpoint (change in CBF) will be assessed by sensor-tipped guide wires during vessel occlusion with a balloon catheter for 1 min.

Therefore, a standard PCI balloon with a diameter 0.5 mm larger than the diameter of the target vessel is delivered via the FFR guide wire and will be inflated proximal to the coronary lesion within an angiographic healthy coronary segment with a low pressure of 4–6 atm to interrupt antegrade blood flow of the vessel during maximal hyperemia. Contrast dye is injected to show the interruption of the antegrade blood flow. During the measurement, the blood pressure of the target vessel distal to the coronary stenosis is continuously monitored as well as the systemic blood pressure.

To differentiate if the results after 4 weeks of therapy are due to CAD or physiological adaptations, the same measurements will be performed in a coronary vessel free of coronary stenosis (the reference vessel).

After 4 weeks of treatment, measurements will be repeated in the same coronary segments.

Cardiac catheterization as well as measurement of the CBF will be performed by three very experienced invasive cardiologists with expertise in hemodynamic analysis. Nevertheless, the procedure may carry some risks such as dissections of the coronary artery by the pressure wire, development of the thrombus burden, stroke or myocardial infarction during vessel occlusion. Application of adenosine intravenously can result in a complete atrioventricular block with short asystole.

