### Assessment of clinical symptoms and patient treatment

All patients undergo detailed assessment of medical history as well as physical examination at baseline and after 1, 3, 6 and 12 months. In patients without known diabetes, an oral glucose tolerance test will be performed before inclusion.

At baseline, 1, 3, 6 and 12 months, the angina pectoris status will be documented according to CCS class 1–4 by a physician blinded to the treatment group. In addition, a symptom-limited bicycle ergospirometry and an echocardiography will be conducted.

An OMT is adjusted according to current clinical practice guidelines in each group at least 2 weeks before initial measurements were obtained. Statins, ß blockers, angiotensin-converting enzyme inhibitors or angiotensin-1 antagonists are obligatory. In addition, patients are treated with an antiplatelet therapy with aspirin 100 mg daily or, if the patient has undergone a previous PCI, a dual antiplatelet therapy will be administered according to current guidelines.

All patients enrolled in the study will be followed for 12 months. At any time during the study period, each patient can withdraw the informed consent. A patient with signs of clinically worsening symptoms will be thoroughly evaluated by the investigator, and if clinically indicated a PCI will be performed. In patients presenting with an acute coronary syndrome, a coronary angiography will be performed immediately, and the target lesion will be treated by PCI. The study will be discontinued for a given patient if continuing would result in a significant safety risk.

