### Adenosine MR perfusion imaging (MRI sub-study)

A cine MRI and an adenosine perfusion MR will be performed at baseline, 4 weeks and 12 months. The aim of this sub-study is to investigate whether MR perfusion imaging can predict myocardial perfusion defects, collateral circulation, LV function and volumes after 4 weeks of exercise training compared to a sedentary control group.

Imaging will be performed with a 1.5-T scanner (Philips Intera CV, Best, The Netherlands) in a standard fashion. After 4 min of adenosine infusion, a perfusion sequence will be started according to a standard protocol. All measurements will be performed by blinded operators with excellent intra- and interobserver variabilities and excellent reproducibility. Exclusion criteria for the MRI sub-study are (1) severe claustrophobia, (2) implantable pacemaker and defibrillator, and (3) contraindications for adenosine (first and second degree AV block, sick sinus syndrome, long QT syndrome, asthma bronchiale).

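### Blinded assessment is stated for angina class, MRI and IVUS but not for the primary endpoint, and no rule says which part of the occlusion trace supplies its value

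*Protocol article*

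**What the plan says.** The Abstract describes a "three-armed randomized, prospective, single-center, open-label, controlled study enrolling 60 patients". The primary endpoint (Primary and secondary outcomes) is "the change in the coronary CBF index after 4 weeks of therapy among the three treatment groups". It "will be assessed by sensor-tipped guide wires during vessel occlusion with a balloon catheter for 1 min" (Measurement of the coronary collateral circulation). The same section says who measures it: "Cardiac catheterization as well as measurement of the CBF will be performed by three very experienced invasive cardiologists with expertise in hemodynamic analysis". Nothing there mentions blinding, a core laboratory or a separate reading of the pressure traces.

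Blinding is stated for other outcomes:

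- Angina (CCS) class is documented "by a physician blinded to the treatment group" (Assessment of clinical symptoms and patient treatment).
- For the MRI sub-study, "All measurements will be performed by blinded operators with excellent intra- and interobserver variabilities".
- The Discussion grants that blinding might have been useful and gives as examples of bias reduction "the use of a central computerized randomization system and a blinded MRI and IVUS core laboratory".

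**The concern.** The article attaches blinding to three lesser outcomes and gives none for the one that carries the conclusion. Central randomization protects the allocation; it does not protect a measurement taken 4 weeks later. A pressure sensor is objective, but a single occlusion pressure still has to be extracted from a trace recorded over a minute, and no rule for doing so is given. If the person extracting it knows the arm and expects exercise to help, readings could drift in that direction in the two exercise arms. Such drift would be indistinguishable from a treatment effect on the primary endpoint. The Discussion hopes the method will separate even small effects, which is where a small reading bias does most harm.

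**Working it through.** **1. Blinding by outcome, as stated in the article**

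| Outcome | Role | Stated assessor | Blinding stated? |
|---|---|---|---|
| CBF index | Primary | Three invasive cardiologists | No |
| MRI perfusion | Secondary | Blinded operators; core laboratory | Yes |
| IVUS virtual histology | Secondary | Core laboratory | Yes |
| CCS class | Clinical follow-up | Physician | Yes |
| QCA | Supporting | Two independent operators | Independent, not blinded |

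**2. What is fixed in the CBF procedure and what is not**

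Fixed in Measurement of the coronary collateral circulation: balloon 0.5 mm larger than the vessel, inflation at 4–6 atm, placement in a healthy segment proximal to the lesion, contrast check of the occlusion, 1 minute of occlusion, maximal hyperemia, and the same segments at 4 weeks. Measurement of FFR fixes the route and rate of adenosine and about 2 minutes to steady state. Not fixed: which part of the continuously monitored 1-minute trace supplies the occlusion pressure.

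**3. Sensitivity of the index to the reading**

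The Background (Assessment of the collateral blood flow) gives index = (P_occlusion − CVP)/(P_ao − CVP). I assume the trial uses this form. A shift d in P_occlusion changes the index by d/(P_ao − CVP). The article gives no pressures, so these are assumed: P_ao 85 to 90 mmHg, CVP 6 mmHg, d = 3 mmHg.

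- P_ao = 85: 3/(85 − 6) = 3/79 = 0.038
- P_ao = 90: 3/(90 − 6) = 3/84 = 0.036

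The Background cites 0.25 as the level separating low from well-developed collaterals. That is a prognostic level, not a yardstick for change, so it gives only a rough sense of scale.

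**4. Effect of a reading bias on the planned test**

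From the article: 20 patients per arm, Kruskal-Wallis test. Assumed: 5% level, normally distributed changes, no true effect, and the same upward bias in every patient of both exercise arms (20,000 simulated trials per row).

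| Bias (SD of change) | Rejection rate |
|---|---|
| 0 | 5.0% |
| 0.10 | 5.7% |
| 0.25 | about 11% |
| 0.50 | about 32% |
| 0.75 | about 63% |

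**5. Steps 3 and 4 cannot be joined from the article**

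No SD of the change is given. A shift of about 0.037 would be roughly 0.75 SD if that SD were 0.05 (0.037/0.05 = 0.74), 0.37 SD if it were 0.10, and 0.25 SD if it were 0.15. These SDs are assumptions with no support in the text.

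**The case against.** The strongest reply is that this argues from silence. The Discussion introduces its measures only as examples, and the list is demonstrably incomplete: blinded CCS grading appears elsewhere in the article but not there. A journal article also leaves detail to the full protocol, and trace-reading procedures could sit there. This has weight. It limits the point to blinding that is not described and does not show that blinding was absent. It does not dispose of the point, because the article raises blinding itself, states it for three other outcomes and describes the CBF measurement at length.

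Second, the procedure is well standardised and the endpoint is a ratio of sensor pressures, less subjective than an image or a symptom grade. That stands for balloon size, inflation pressure, segment and occlusion time. It does not cover the choice of reading window. The reference-vessel measurement is no substitute for blinding, since no separate assessor is named for it.

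Third, the bias sizes are assumed, and at 0.10 SD the false-positive rate barely moves. That is correct; the figures are illustrations only.

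Two stronger readings are tempting. A reader might infer that the cardiologists know the allocation; the article never says so. A reader might also infer that any bias would be beyond repair; that does not follow, because stored traces could be re-read blind. Only bias introduced during the catheterization itself would remain.

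**Conclusion.** The point holds as a gap in what is stated: the primary endpoint has no described blinded assessment and no rule for selecting the occlusion pressure from the trace, while three other outcomes are described as blinded. It does not show that the operators were unblinded or that the result is biased. That the trial is a declared proof-of-concept study and acknowledges the lack of blinding lessens the force of the point but does not close the gap.

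The size is conditional. A 3 mmHg reading shift is worth about 0.036 to 0.038 on the index under the assumed pressures. The false-positive rate would be about 11% to 63% for a uniform bias of 0.25 to 0.75 SD in both exercise arms. Neither figure estimates what happened in this trial. The plan should be changed because the remedy is cheap and concerns the primary result.

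**What to change.** Define the primary CBF value as an offline reading of the stored pressure traces. Code the traces so that arm and visit are hidden, and use one occlusion window written down before any reading. The reader should be one of the existing three cardiologists who did not perform that procedure. If two of them did a patient's two visits, the third can still read both. If a blinded reading is already in place, one sentence saying so, together with the window rule, settles the matter.

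The cost is reading time: 60 patients × 2 visits × 2 vessels (target and reference) = 240 one-minute traces. No new procedure, patient or assessor is needed. It works only if the traces were stored; the article says that pressures are continuously monitored, not that they are kept.

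Blinded reading cannot correct bias arising during the procedure, such as in balloon placement or in judging hyperemia. Reassigning the 4-week operators is probably too late: recruitment was expected to finish by June 2012 and the article is dated September 2012. This part should be reported as a remaining limitation.

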## Conclusion

Exercise training results in an increased delivery of blood to myocardial regions in need, but the pathophysiology is still unclear.

The Excite trial was designed to investigate whether intensive exercise training for 4 weeks as IT and MT in comparison to a sedentary control group with OMT only will increase the coronary collateral circulation in patients with stable CAD and significant epicardial stenosis (FFR ≤ 0.75).

## Trial status

Recruitment has commenced in June 2009. We expect to complete recruitment by June 2012. Final results (12-months clinical endpoint) are planned to be published in July 2013.

## Abbreviations

ADMA: Asymmetric dimethylarginine; CAD: Coronary artery disease; CBF: Coronary collateral blood flow; CI: Confidence interval; EPC: Endothelial progenitor cells; ET: Exercise training; FFR: Fractional flow reserve; IT: High-intensity interval trainings; IVUS: Intravascular ultrasound; MACE: Major adverse cardiovascular events; MRI: Magnet resonance imaging; MT: Moderate-intensity exercise training; OMT: Optimal medical therapy; PCI: Percutaneous coronary intervention; QCA: Qualitative comparative analysis; VEGF: Vascular endothelial growth factor.
